##### Performance feedback

The CM Competence Scale [39], a fidelity scale measuring nine key CM session elements and three general CM skills, will be provided during the didactic training along with a rating manual. This scale will be used to guide provision of performance feedback. Items are scored on 7-point Likert scales: an average score of 4.0 out of 7.0 is considered an adequate fidelity score [34].

During the preparation phase, all OTP counselors will receive performance feedback on two practice cases using the CM Competence Scale. First, the role plays at the end of the training workshop will be observed by CM experts on the research team to determine if each counselor demonstrated adequate fidelity. Live performance feedback will be provided immediately after each role play. Counselors who do not exhibit adequate fidelity during the live role-play will be given corrective feedback and the opportunity to complete another role play until each element of the CM Competence Scale is covered. Second, counselors will have 1 month following the workshop to submit an audio recording of a role-played CM session, with another CM counselor or leader at their OTP. Role plays will use a standardized patient script and be rated by blind coders. CM counselors who demonstrate satisfactory competence will be given positive performance feedback whereas those counselors who do not will be given corrective feedback. OTP leaders will be encouraged to complete fidelity ratings of two role-play sessions to gain familiarity with using the CM Competence Scale as a performance feedback tool.

Additional feedback will be provided via a 20-item CM Knowledge test. CM counselors scoring ≤ 16 (75%) on their test will receive corrective feedback. Leaders will receive a group-level summary of CM Knowledge scores by item for their OTP, to identify areas in need of further training or remediation.

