##### Performance feedback

CM fidelity monitoring will be enhanced by the CM Tracking Tool, an Excel tracking tool developed by the study team. The tool prompts counselors to complete a brief Weekly Report for each CM patient. Each report takes 2–3 min to complete and collects date of the CM session; results of the stimulant urine screen; number of CM draws administered; and specific draws received. It also contains the first 6 items of the CM Competence Scale, which counselors complete as a self-reported fidelity check. Data input into the CM Tracking Tool yield a user-friendly dashboard for counselors that shows each patient’s progress through the CM program, summarizes fidelity of CM delivery, and automatically calculates the number of draws earned and number of draws anticipated in the next session. The CM Tracking Tool is used as the basis of a recommended EMR build for the OTPs and serves as a viable low-tech alternative.

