#### EMR extraction and CM tracking tool

OTPs will document CM session delivery in their usual session records within their existing EMR systems and extract a de-identified dataset including all patient encounters at six time points (start and end of each wedge). OTPs will also be given the Excel CM Tracking Tool to facilitate ongoing tracking and provision of real-time feedback, and those OTPs that opt to use the tool will be asked to send the Excel tracker at the same six time points. De-identified data from all available patient records will be identified by each site to allow the study team to calculate key study variables at each OTP including reach, effectiveness (patient abstinence and treatment retention), adoption, implementation, and maintenance.

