#### Research team observational measures

Research staff will complete observational measures of implementation strategy progress (on an ongoing basis) and counselor fidelity to the CM model (at the end of the didactic workshop). These scales will enable us to examine the concordance between provider-self report and research staff observation.

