### Study measures

To address Specific Aim 1 (implementation effectiveness), we measure the following implementation outcomes: Reach, Adoption, Implementation, Maintenance, and Equity [45]. To evaluate Specific Aim 2 (patient effectiveness), we measure two patient outcomes in line with the Effectiveness element of RE-AIM: Stimulant Abstinence and Treatment Retention. Finally, in pursuit of Specific Aim 3 (exploratory mediators), we evaluate contextual determinants as putative mediators of implementation outcomes; specifically, we assess implementation strategy progress, inner setting factors, and provider characteristics. Table 1 presents a detailed overview of study measures by Specific Aim.

**Table 1 Tab1:** Description of study measures, data source, and timing of measurement

Outcome	Definition	Data source	Frequency and timing of measurement
*Aim 1*			
Reach	Calculates patients’ exposure to contingency management (CM) by dividing the number of newly admitted patients with recent stimulant use (defined as documented patient-reported stimulant use or a positive stimulant urine screen within the first 30 days of treatment) who received 1 or more CM encounters by the total number of newly admitted patients with recent stimulant use.	Electronic medical records (EMR) CM tracking tool	End of each wedge
Adoption	Calculates the proportion of providers who have adopted CM by dividing the number of counselors who delivered 1 or more CM encounters divided by the total number of counselors.	EMR CM tracking tool	End of each wedge
Implementation	Assesses delivery of CM with fidelity in two ways: 1. Proportion of counselors meeting the fidelity target on the CM Competence Scale (a mean overall score ≥ 4.0), which rates 9 CM elements on a scale from 1 (not at all present) to 7 (fully present) 2. Proportion of CM sessions covering ≥ 7 of 9 of the standard CM elements, as assessed by a self-report checklist in the CM tracking tool.	Observer rating CM tracking tool	Role play following Preparation phase End of each wedge
Maintenance	Measures Reach, Adoption, and Implementation throughout the Sustainment phase.	EMR CM tracking tool Observer rating	End of each wedge during Sustainment phase
Equity	Evaluates whether the above systematically vary based on race/ethnicity, biological sex, gender, and other sociodemographic factors of patients and providers.	EMR Provider survey	Baseline
*Aim 2*			

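### Table 1 requires at least 7 of 9 elements for session-level CM fidelity, but the tracking tool that supplies the count is described as holding six fidelity items

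*Protocol article*

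**What the plan says.** Table 1 (Study measures, Aim 1) gives Implementation two fidelity measures.

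- **Measure 1** is the proportion of counselors reaching a mean of at least 4.0 on the CM Competence Scale. Its source is observer rating of a role play after the Preparation phase.
- **Measure 2** is the proportion of CM sessions covering at least "7 of 9 of the standard CM elements, as assessed by a self-report checklist in the CM tracking tool". Its source is the CM Tracking Tool, at the end of each wedge.

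The tool is described under Performance feedback in the Implementation phase. Its weekly report "collects date of the CM session; results of the stimulant urine screen; number of CM draws administered; and specific draws received". On fidelity, the text says: "It also contains the first 6 items of the CM Competence Scale, which counselors complete as a self-reported fidelity check".

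The scale itself is introduced under Performance feedback in the Preparation phase as "a fidelity scale measuring nine key CM session elements and three general CM skills".

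Table 1's Maintenance row carries Implementation forward: "Measures Reach, Adoption, and Implementation throughout the Sustainment phase". Its Equity row asks whether the preceding outcomes vary with patient and provider characteristics.

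On data return, the section on EMR extraction says that "those OTPs that opt to use the tool will be asked to send the Excel tracker".

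**The concern.** The outcome rule and the instrument that feeds it do not fit. A rule that needs seven affirmed elements cannot be met from a form that asks about six. Measure 2 is the only measure of fidelity in delivered CM sessions, because measure 1 rests on role plays.

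If both statements are followed literally, the measure takes the value zero wherever it can be computed and says nothing about how CM was delivered. If the mismatch is noticed only after CM delivery has begun, the team would have to choose a new threshold with data in hand. If the form really has six items, answers to the three missing ones could not be recovered from completed weekly reports.

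**Working it through.** The protocol states no expected rate, sample size or power for this measure (Table 2 lists no comparison for Implementation). There is therefore no planned figure to reproduce, and the check is a count.

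**Inputs**

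| Input | Value | Where |
|---|---|---|
| Elements required for a session to qualify | at least 7 of 9 | Table 1, Implementation, measure 2 |
| Items in the tool's self-report fidelity check | 6 | Implementation phase, Performance feedback |
| Full CM Competence Scale | 9 CM elements + 3 general skills = 12 items | Preparation phase, Performance feedback |

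**Step 1: can the threshold be reached?** Most that can be recorded = 6. Required = 7. Shortfall = 7 − 6 = 1. As shares of nine, 6/9 = 66.7% and 7/9 = 77.8%. The chance of at least 7 affirmed among 6 items is 0 whatever the coverage per item (checked at 0.5, 0.9, 0.99 and 1.0).

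**Step 2: could another source supply elements seven to nine?**

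- The tool's other fields are the session date, screen result, number of draws and the draws received. Nothing says that they are scored as fidelity elements.
- Research staff rate "counselor fidelity to the CM model (at the end of the didactic workshop"), and the other rated recordings are role plays. Neither is a rating of a delivered patient session.
- Table 1 lists observer rating and the tracking tool as the sources for Implementation. It does not list the EMR. The recommended EMR build is itself based on the tool.
- No second per-session checklist is described.

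**Step 3: would the rule work on nine items?** Assume, for illustration only, that each element is covered independently with probability 0.9:

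P(at least 7 of 9) = 36 × 0.9⁷ × 0.1² + 9 × 0.9⁸ × 0.1 + 0.9⁹ = 0.172 + 0.387 + 0.387 = 0.947 (unrounded sum).

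At a coverage of 0.5 the chance is 0.090. The rule is usable on nine items and separates high from low coverage.

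**Step 4: what is the nearest rule on six items?** 7/9 × 6 = 4.67, so the nearest whole count not below it is 5, and 5/6 = 83.3%. Under the same illustrative coverage of 0.9:

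P(at least 5 of 6) = 6 × 0.9⁵ × 0.1 + 0.9⁶ = 0.354 + 0.531 = 0.886 (unrounded sum).

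This is below 0.947, so 5 of 6 is somewhat stricter. It also leaves three elements unmeasured.

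**Step 5: what depends on measure 2?** The Aim 1 hypothesis names Reach, Adoption and Maintenance, and there defines Maintenance by reach and adoption alone. The Aim 1 models in Data analysis cover the same three outcomes. Only Table 1's wider Maintenance row, and its Equity row, reuse measure 2.

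**The case against.** The strongest reply is that the documents show a conflict, not an unusable form. The tool description does not say that six items are all the form will ever hold. If the Excel form has nine elements, the description is a one-line error and no session fails for this reason. That stands: the documents cannot show which statement is wrong, only that both cannot be right.

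It can also be said that little rests on this measure. That stands too. It is outside the Aim 1 hypothesis, has no powered comparison, and is one of two fidelity measures, the other being unaffected.

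Three stronger readings are tempting, and the documents do not support them:

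- **That the outcome would be 0% at every OTP in every wedge.** The tool is described from the Implementation phase onward and stays available in Sustainment. No tool-recorded sessions are described before crossover, so the proportion there is undefined, not zero.
- **That the measure exists only at OTPs that opt in to the Excel tool.** The tool is also the basis of a recommended EMR build, and the EMR extraction section expects implementation to be calculable at each OTP. Sites without the Excel form may capture the same fields. However, that build is only recommended, and Table 1 does not name the EMR as a source for Implementation. Coverage of sites is therefore uncertain, but its loss is not shown.
- **That the hypothesised Maintenance outcome is compromised.** As hypothesised in the Background, Maintenance excludes Implementation. Only Table 1's broader definition is affected.

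Nor does the text show that the threshold would be changed after the data are seen. That is a risk if nothing is done.

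**Conclusion.** The inconsistency is real. With the instrument as described, the maximum is 6 against a required 7, so no recorded session can meet the session-fidelity criterion. This rests on one reading: that Table 1 and the tool description refer to the same self-report check. Both place it in the CM Tracking Tool, and no other is described.

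The damage is confined to session-level fidelity, a descriptive Aim 1 measure, and to its reuse in Table 1's Maintenance and Equity rows. Observer-rated measure 1, the Reach and Adoption hypotheses, the Aim 2 outcomes and every power figure in Table 2 stand. A full protocol or analysis plan would not dissolve the point, because two explicit statements in this article disagree and one needs correcting. It should be fixed, but it does not threaten the trial's main conclusions.

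**What to change.** Trial status says that no organization or provider was enrolled at writing, so all of this can precede data collection. Before the first wedge:

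1. **Check the tool.** If its self-report check holds all nine CM elements, correct the tool description under Performance feedback. Cost: one sentence.
2. **If it holds six, preferably add the three missing CM-element items** to the weekly report and to the recommended EMR build, and keep 7 of 9. Cost: three items in an Excel form and slightly more counselor time per report, now put at 2–3 minutes.
3. **If six items must stay, pre-specify a threshold on six items in Table 1**, for example at least 5 of 6. State that this is a somewhat stricter share (83% against 78%) and a narrower construct. Cost: one line, and the loss of three elements from the measure.
4. **Report which OTPs contribute data to this measure**, and whether by the Excel tool or the EMR build. If the EMR build is to count as a source, name it in Table 1. Cost: one line in the plan and one in the report.

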The SSL has demonstrated effectiveness in promoting the implementation of CM targeting attendance [20], but has never been evaluated for the implementation of CM targeting stimulant use. Furthermore, prior SSL studies have been subject to several limitations. First, previous investigations have confounded receipt of the SSL implementation strategy with provision of CM resources by providing OTPs a fully stocked prize cabinet at the start of implementation [20, 21, 24]. Second, SSL trials have only measured sustainment for up to 6 months [24], which limits conclusions about the ability of OTPs to continue CM implementation without active support. Finally, studies of the SSL have not rigorously tracked adherence to implementation strategy [20, 21, 24]. The current project will address these three gaps by: decoupling the SSL strategy from the provision of incentives; using a stepped wedge design that enables monitoring of sustainment over a longer time horizon; and rigorously specifying and tracking the SSL strategy.

Our protocol is guided by three specific aims:Specific aim 1 (primary aim): to test the effectiveness of the SSL on implementation outcomes. It is hypothesized that receipt of the SSL will be associated with significant increases in: CM Reach (percent of patients receiving CM), CM Adoption (percent of providers delivering CM), and CM Maintenance (reach and adoption after removal of active support).Specific aim 2 (secondary aim): to test the effectiveness of the SSL on patient outcomes. It is hypothesized that receipt of the SSL will be associated with significant increases in: Stimulant Abstinence (percent of stimulant-negative screens) and Treatment Retention (number of treatment sessions).Specific aim 3 (exploratory aim): to evaluate contextual determinants, including SSL adherence, as putative mediators of implementation outcomes. It is hypothesized that contextual factors at the organization-level (e.g., implementation climate, leadership) and provider-level (e.g., perceptions of CM) will partially explain the effect of the SSL on implementation (Aim 1) outcomes.

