### CM intervention

The CM protocol that will be implemented is Petry’s evidence-based low-cost CM targeting stimulant abstinence [10, 33, 34], which provides immediate reinforcement via prize draws on an escalating schedule. We chose this CM model because of literature supporting better outcomes for patients with stimulant use when: reinforcement is provided immediately [35]; abstinence is the target [36]; and incentive values escalate to promote retention and enhance the patient’s motivation over time [35, 37, 38]. We simplified Petry’s schedule based on formative research with OTP providers who requested simple, weekly draws [13] and a prize system that could be feasibly sourced (i.e., gift cards).

For this study, partner OTPs will administer one random toxicology screen to CM patients per week for 12 weeks. OTPs may choose to test other substances, but reinforcement will be contingent on a negative stimulant result. OTPs may choose which provider (e.g., nurse, counselor) will administer the screen. The CM counselor of record will review the results with the patient.

Patients will earn prize draws for each stimulant negative sample. Draws increase by one for each negative screen for 12 weeks, yielding a maximum of 78 draws for patients who submit 12 negative samples (i.e., 1 + 2 + 3 + 4 + 5 + … + 11 + 12). A refused or missed screen (i.e., unexcused absence on a testing day) resets draws for the next negative sample down to one, with draws again escalating for sustained abstinence. Patients draw prizes from fishbowls containing 500 slips of paper; 250 state “good job!” but are not associated with a prize, 209 state “small,” 40 state “large,” and one “jumbo.” Using these probabilities and magnitudes of $5, $25, and $100 for the three respective prize sizes, each draw has an average cost of $4.21. Thus, for a 12-week protocol, patients maintaining abstinence would be expected to earn an average of 78 draws × $4.21 draw = $328 in prizes. This maximum anticipated earning rate is identical to the rate used by [name] team in the VA rollout [10]. Of note, the average cost of CM in the VA was only $150 per patient, due to missed sessions resulting in resets back to 1 draw [10]. Ensuring OTPs can sustain this investment after removal of support is a key aspect of SSL external facilitation.

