Stimulant abstinence	Calculates abstinence rates as the number of urine screens that are negative for stimulants divided by the total number of urine screens received by patients with recent stimulant use.	EMR	End of each wedge
Treatment retention	Measures engagement with treatment in three ways for each patient: 1. Duration of time from patient intake to discharge in day 2. Proportion of scheduled encounters that the patient attended 3. Number of CM sessions received	EMR EMR CM tracking tool	End of each wedge
*Aim 3*			
*Implementation strategy progress*			
Stages of Implementation Completion (SIC) [46]	Evaluates completion of key activities for implementing the contingency management intervention across 8 stages. Two scores are calculated for each stage: proportion calculates the percent of activities completed within a stage and duration calculates time from date of entry through completion.	Process notes External facilitator report	Ongoing throughout Preparation and Implementation phase for each OTP
Cost of Implementing New Strategies (COINS) [47]	Calculates the fees, expenses, and person hours necessary to complete the implementation strategy as mapped onto SIC. Customized via a standardized adaptation approach.	Process notes External facilitator report	Ongoing throughout Preparation and Implementation phase for each OTP
*Inner Setting Factors*			
Implementation Climate Scale (ICS) [48]	Measures provider perceptions of the extent to which organizations expect, reward, and support implementation of CM. Scale includes 18 items scored on 5-point scales from 0 (not at all) to 4 (very great extent) divided into 6 subscales.	Provider surveys	Three timepoints for each OTP crossing into active support: Start of Preparation, Midpoint of Implementation, End of Implementation
Implementation Leadership Scale (ILS) [49]	Measures providers’ report of the extent to which leaders at their organization are aligned and visibly in support of CM. Scale includes 12 items, rated from 0 (not at all) to 4 (very great extent) divided into four subscales.	Provider surveys	Three timepoints for each OTP crossing into active support: Start of Preparation, Midpoint of Implementation, End of Implementation

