### Data analysis

Across 2400 EMR pulls, 720, 480, and 1200 are expected to occur during Usual Care, Preparation/Implementation, and Sustainment phases, respectively. Preliminary analysis will include bivariate and multivariate analysis using correlations, cross-tabulations and regression models to ascertain data structure, statistical distribution, and study artefacts. Analyses for all Aims will be performed using multilevel structural equation models (MSEM) in Mplus 8.10 [51]. We conducted Monte Carlo simulation power analyses modeling treatment effects and outcome variance nested in OTPs (anticipated ICC: 15%) and/or counselors (anticipated ICC: 10%; see Table 2). There is no expected missing data from EMR pulls, although at OTP and counselor levels, analyses will follow an intent-to-treat approach to dealing with missing data. Across all analyses, we will employ a moderator-first approach to the equity of treatment effects to ensure that group-level differences can be validly interpreted and that we are sensitive to differential treatment effects among patient subgroups. Similarly, we will examine whether significant variance in treatment effects occurs at counselor- or OTP-levels (through exploring the size of random effects variance parameters) before concluding whether treatment effects can be validly interpreted as fixed at the patient-level.

**Table 2 Tab2:** Results of Monte Carlo simulation analyses examining power to detect aim 1 and aim 2 outcome effects

Outcome	Comparison (*n* per condition)	Predicted rates/effects	Power at α = .05
*Aim 1*			
Reach^a^	Usual care (720)–preparation/implementation (480)	2–22%	98%
Adoption^b^	Usual care (70)–preparation/implementation (70)	10–50%	95%
Implementation	No comparison		
Maintenance	Preparation/implementation (480)–sustainment (1200)		
*Aim 2*			
Stimulant abstinence	Usual care (720)–preparation/implementation (480)	25–40%	90%
Treatment retention	Usual care (720)–preparation/implementation (480)	9 weeks–12 weeks	94%

Monte Carlo simulation multilevel power analyses featuring clustering in opioid treatment programs (anticipated ICC: 15%) and/or counselors (anticipated ICC: 10%)

^a^Assessed among patients nested in counselors and opioid treatment programs

^b^Asssessed among counselors nested in opioid treatment programs

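### Stimulant abstinence is defined over screens received while CM itself sets how often patients are screened, so the Aim 2 contrast can shift in either direction with no change in use

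*Protocol article*

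**What the plan says.** - **Definition.** The Stimulant abstinence row of Table 1 (Study measures) gives this ratio for the outcome: "number of urine screens that are negative for stimulants divided by the total number of urine screens received by patients with recent stimulant use". The aims at the end of the Background also express it as a percentage of screens. The population is all newly admitted patients with recent stimulant use, whether or not they receive CM.
- **Neighbouring row.** Treatment retention, by contrast, "Measures engagement with treatment in three ways for each patient", and one of those three measures uses scheduled encounters as its denominator.
- **Testing schedule.** Under CM intervention, "partner OTPs will administer one random toxicology screen to CM patients per week for 12 weeks". The article gives no schedule for usual-care patients or for patients in the SSL phase who do not receive CM.
- **Missed screens.** "A refused or missed screen (i.e., unexcused absence on a testing day) resets draws for the next negative sample down to one". This governs draws; the outcome definition has no rule for a missed screen. The same section reports that "the average cost of CM in the VA was only $150 per patient, due to missed sessions resulting in resets back to 1 draw", against an expected $328 for sustained abstinence.
- **Planning figures (Data analysis, Table 2).** Abstinence 25% to 40%, 720 against 480, power 90%. Reach 2% to 22%.

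**The concern.** The strategy under test raises the share of patients on CM, and CM brings weekly screening. A denominator of screens received therefore depends on condition in two ways. Patients on CM contribute more screens than others, so their results carry more weight in a pooled ratio. Any screen that is missed or refused also leaves the ratio altogether. If CM recipients differ from other patients in underlying use, or if CM changes how often would-be-positive screens are skipped, the ratio changes although nobody's use has changed.

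At stake is the interpretation of one of the two Aim 2 patient outcomes. As worded, neither a positive nor a null result separates changed use from changed testing. This is a definition the article states, so an analysis plan that follows it would inherit the problem.

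**Working it through.** **The plan's own figure.** A plain two-proportion test of 25% against 40% with 720 and 480 has 99.98% two-sided power. Stepped-wedge approximations (10 OTPs, five six-month periods, 48 patients per OTP per period, OTP ICC 0.15, counselor ICC 0 or 0.10) run from 53% to above 99%, depending on period effects and between-period correlation. The stated 90% lies inside that range. The simulation settings are not complete enough to reproduce it, and nothing here shows it to be wrong.

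**Unit behind 720 and 480.** Participant recruitment expects about 8 patients per month per OTP: 8 × 10 × 30 = 2400. Data analysis splits this as 720 + 480 + 1200 = 2400. Table 2 therefore counts patients, while Table 1 counts screens.

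**Inputs from the article.** Reach r = 0.22; 12 screens per CM patient; patient-average true negativity 25% in both conditions (no effect).

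**Assumed inputs.** k = routine screens per other patient over the same 12 weeks, 3 or 6; p_c = true negative rate among CM recipients; s = share of would-be-positive CM screens skipped, with no skipping elsewhere unless stated. The 2% usual-care Reach is ignored. Reach counts anyone with one CM encounter, so 12 screens for each is the full schedule and an upper figure.

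**Formulas.** For the others, p_o = (0.25 − r·p_c)/(1 − r). The pooled SSL-phase ratio is

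[12r·p_c + (1−r)k·p_o] / [12r(p_c + (1−p_c)(1−s)) + (1−r)k].

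Here 12r = 2.64, and (1−r)k = 2.34 (k = 3) or 4.68 (k = 6). CM patients supply 2.64/4.98 = 53% or 2.64/7.32 = 36% of screens while being 22% of patients.

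**Results** (usual care reads 25% throughout):

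| Scenario | k = 3 | k = 6 |
|---|---|---|
| Frequency alone: p_c = 0.25, s = 0 | 25.0% | 25.0% |
| CM to lower-use patients: p_c = 0.40, p_o = 0.208 | 1.542/4.98 = 31.0% | 2.028/7.32 = 27.7% |
| CM to heavier users: p_c = 0.15, p_o = 0.278 | 1.047/4.98 = 21.0% | 1.698/7.32 = 23.2% |
| Skipping alone: p_c = 0.25, s = 0.30 | 1.245/4.386 = 28.4% | 1.830/6.726 = 27.2% |
| p_c = 0.40 and s = 0.30 | 1.542/4.505 = 34.2% | 2.028/6.845 = 29.6% |

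Selection with equal testing (k = 12) also returns 25.0%. Frequency and selection therefore bias the ratio only jointly; differential skipping does so alone.

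**Skipping in both conditions.** With 30% of would-be-positive screens skipped everywhere, both conditions read 0.25/0.775 = 32.3%, so the difference is zero. If CM lowers skipping to 10% while it stays at 30% elsewhere, the SSL phase at k = 3 reads 1.245/(2.64 × 0.925 + 2.34 × 0.775) = 1.245/4.256 = 29.3% against 32.3%: a bias against SSL.

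**Each patient weighted equally.** Both selection scenarios return to 25.0%. Skipping under CM only gives 0.22 × 0.25/0.775 + 0.78 × 0.25 = 26.6%, a residual of 1.6 points against 3.4 pooled at k = 3. With 10% against 30% skipping the result is 0.22 × 0.270 + 0.78 × 0.323 = 31.1% against 32.3%, a residual of about −1.2 points against −3.0 pooled.

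**The case against.** **The pooled ratio is an inference.** Table 1 also writes Reach and Adoption as simple ratios, yet the footnotes to Table 2 analyse them on patients and counselors in multilevel models. Aim 2 is to be fitted with generalized MSEM, and Table 2 counts patients. A patient-level analysis may well be intended. This largely stands: the unit is unsettled, and a patient-level analysis would remove the frequency weighting. It would not recover missed screens, and it would still disagree with the screen-based definition.

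**A reader might infer that the contrast is biased towards SSL.** The article does not support that. It does not say who will be offered CM, and the reset rule penalises a missed screen, so CM could reduce skipping. The same arithmetic gives bias against SSL in both of those cases.

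**A reader might infer that the artefact is as large as any plausible real effect.** The planned effect is 15 points, and the scenarios tabulated above move the ratio by between −4.0 and +9.2 points. A smaller benchmark of 0.20 × 15 = 3 points arises only if the 15 points are read as the effect per CM recipient, which the article does not say.

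**A reader might take "There is no expected missing data from EMR pulls" as a rule for untested weeks.** It is about extracting records. It neither creates nor solves the problem.

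**Rank.** The outcome belongs to the secondary aim of a type 3 hybrid trial that gives priority to implementation outcomes. That stands and limits the severity.

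**Conclusion.** The concern holds in conditional form. The article fixes screens received as the denominator and specifies a testing schedule for CM patients only, so a ratio pooled over screens can differ between conditions with no change in use. The direction is not determined. At 22% Reach and 3 (6) routine screens per other patient, the shift is +6.0 (+2.7) points if CM recipients average 40% negative, −4.0 (−1.8) if they average 15%, and +3.4 (+2.2) if 30% of would-be-positive screens are skipped under CM only. Routine testing frequency, patient mix and skipping rates are assumptions; the article gives none of them. Separately, and without any assumption, the screen-based definition and the patient counts in Table 2 do not agree and must be reconciled. The definition should be fixed, but the primary aim is not affected.

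**What to change.** Define abstinence per patient, with every eligible patient weighted equally over the same fixed period after intake in all conditions, and state the patient as the unit so that Table 1 and Table 2 agree. Report screens per patient by condition, including the number of patients with none. Add sensitivity analyses for missed screens, for example missed scheduled CM screens counted as positive, and CM patients' screens thinned to the routine testing frequency.

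Do not make a rule that counts an empty time window as not negative the main analysis, because it penalises the less-tested usual-care condition. With three windows and 3 randomly timed routine screens, (2/3)³ = 30% of routine windows are empty. Usual care then reads 0.25 × 0.704 = 17.6% and the SSL phase 0.22 × 0.25 + 0.78 × 0.176 = 19.2%, which favours SSL by 1.6 points with no effect and no skipping. If the first screen received in each window is used and 30% of would-be-positive screens are skipped under CM, the artefact is 3.2 points, almost the 3.4 of the pooled ratio.

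The cost is rewording. The extract already covers all patient encounters, and the Trial status section says that no organization had been enrolled. The downside is that the extra weekly CM screens get less weight and some bias from skipped screens remains, to be bounded by the sensitivity analyses.
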